### Chewing gum administration

Green PK brand of chewing gum will be used in this study since a pilot survey done before data collection showed that majority of the people preferred the green flavor (*appendix II, unpublished data*). We will use one flavor to minimize bias. The patients in Group A will be given green flavored PK and will start chewing after regaining consciousness. The patients will chew 2 pellets of PK till they are tasteless three times in a day (morning, afternoon, and evening). After chewing, the patients will be encouraged to rinse the mouth with clean water. The patients will stop chewing gum when POI resolves. Resolution of POI will be defined as passage of stool or flatus or both in addition to full filling the criteria defined in the 6 domains described by the Tripartite gastrointestinal recovery post-operative ileus group such as absence of nausea and vomiting, having no need of nasogastric intubation, absence of abdominal pain and distension, and ability to tolerate oral feeds [29]. Each patient will be offered a watch, notebook, and pen and with the help of the caretaker, record every day’s events and the time they occur. The events recorded will include; time when gum is chewed, flatus passed, stool passed, vomited or hunger felt. The outcome assessors will do clinical evaluation 6 hourly and information will be recorded in the data collection form (appendix I).

### Study variables

Primary outcome variable will be time taken from end of surgery to resolution of ileus.

Secondary outcome variables will be duration of hospital stay in days (counted from time of admission to time of discharge), in-hospital morbidity and mortality.

Morbidity will be defined as any deviation from the postoperative course that is not inherent in the procedure and does not comprise a failure of cure and will be reported in accordance with the Clavien Dindo classification 2004 [30]. Grade I: Any complication that does not require additional pharmacological, radiological or surgical intervention, II: Requires pharmacological treatment but not radiological or surgical intervention eg blood transfusion, III: Requires radiological or surgical re-intervention eg endoscopy and IV: Life threatening complications eg atleast one organ failure requiring ICU admission.

### Validity of the data collection tools

A Pilot study was performed to pre-test the questionnaire and confirm its effectiveness, by using a content validity index. Two surgeons in Hoima were given the questionnaire and content validation form was prepared. The surgeons reviewed both the domain and the item and assigned scores. The content validity index was calculated. A content validity index of at least 0.80 was considered acceptable as recommended by Davis [31] after making necessary adjustments.

### Reliability of the data collection tools

Reliability analysis was conducted before starting data collection. A Cronbach’s coefficient alpha of ≥ 0.70 was considered for a questionnaire to be used to collect the data. Such a Cronbach’s coefficient alpha implies the questionnaire elements are reliable and reproducible.

### Data processing and analysis

The intention to treat model will be used during analysis to minimize bias. Summarized data will be analyzed using Statistical Package for the Social Sciences (SPSS Inc., Chicago, USA, version 22.0 for Windows). Continuous variables will be presented as the mean ± standard deviation. Categorical variables will be expressed as frequencies.

To compare the time taken for post-operative ileus to resolve and length of hospital stay, normality of distribution will be assessed using the Shapiro-Wilks test. If the data are found to be normally distributed, then equal variance for the two groups will be determined using Levene’s test hence two sample t-test will be computed assuming equal or unequal variance as appropriate. If the data are not normally distributed in both groups, the nonparametric Wilcoxon Rank sum (Mann-whitney U) test will be used to compare the difference in means. To compare the in-hospital morbidity and mortality, the chi squared test will be used. All analyses will be performed at 95% confidence level and a p value ≤0.05 will be considered significant.

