### Hypotheses

The null hypothesis of this study is that there is no difference in the duration of POI when gum is chewed compared to when it is not.

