### Sample size estimation

Using the formula; 
N = 2\; \times \,{({\textstyle{{{Z_{1 - \alpha /2}}\; + {Z_{1 - \beta }}} \over \delta }})^2} \times {S^2}
 for determining sample size in randomized clinical studies with a statistical superiority design [27], and findings from a study that evaluated effect of chewing gum following pancreatic-duodenal surgery in Sweden [28], 46 participants per group will be required. On adjusting the sample size to the finite population and adding 10% to improve internal validity, the required sample size will be 52.

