## Discussion

Previous researchers have not focused on acute peritonitis due to gastroduodenal perforations when assessing effect of chewing gum on ileus which this study is set to address. In their findings so far, there is compelling evidence to suggest that chewing gum plays a role in resolution of ileus [9,12], although controversial findings have been reported as well [28]. Our study is timely to shade more light in the context of low resource settings that are often under-represented in research publications.

Readily available and affordable chewing gum could offer benefit of reducing prolonged post-operative ileus and result in an added advantage of being discharged through a short-hospital-stay track. This protocol seeks to generate level one evidence regarding the role of chewing gum in resolution of ileus among patients with peritonitis due to gastro-duodenal perforations.

The generalizability of our study is limited by relatively smaller sample size and excluding patients with comorbidities but we hope our findings could be used to benchmark larger future multi center randomized controlled trials. More so, in this study, the participants will be un-blinded early since any placebo in this case would also count as sham feeding. We will only enroll patients with peritonitis due to gastroduodenal perforations which may not have a high bacterial burden compared to other gastrointestinal perforations thus generalizability of results will be limited in this context.

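### On the non-normal branch the plan pairs mean ± SD with a rank-sum test that it describes as a comparison of means, so the summary shown and the p value concern different quantities

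*Protocol article*

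**What the plan says.** The section on data processing and analysis in the protocol article makes three statements that bear on this point.

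- **Summary.** "Continuous variables will be presented as the mean ± standard deviation". No exception is made for skewed data.
- **Test.** For time to resolution of ileus (the primary outcome) and for length of stay, normality is checked with the Shapiro-Wilk test. If the data pass, a two-sample t-test follows, with equal or unequal variances according to Levene's test. If they fail, the Wilcoxon rank-sum (Mann-Whitney) test is used, and its stated purpose is to compare the groups' difference in means.
- **Decision rule.** "All analyses will be performed at 95% confidence level and a p value ≤0.05 will be considered significant".

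The section names no between-group estimate for either outcome. The reference to a 95% confidence level sets the significance level; it does not commit the trial to reporting an interval. The null hypothesis is that "there is no difference in the duration of POI when gum is chewed compared to when it is not", and the main objective is to determine gum's effect on ileus duration.

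**The concern.** A summary and a test should describe the same contrast. On the t-test branch they do: group means and SDs are shown, and the p value concerns the difference between those means. On the rank-sum branch they do not. The rank-sum test asks whether values in one group tend to be larger than values in the other. Its statistic depends only on the ordering of the observations, so a few very long recovery times can move a group mean a great deal while hardly changing the ranks. With skewed data the mean difference and the rank-sum result can disagree in size, and even in direction.

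Times to recovery and lengths of stay are often right-skewed, so the non-normal branch is a realistic route for both outcomes. A reader would then see two means and a p value and would naturally, but wrongly, take the p value as a verdict on the gap between those means. The objective asks for the effect of gum, and the Discussion hopes the findings will serve as a benchmark for larger trials. Both uses need an estimate that belongs to the test performed.

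**Working it through.** **1. What each branch displays and tests**

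| Branch | Summary planned | What the test addresses | Do they match? |
|---|---|---|---|
| Normal: t-test | mean ± SD | difference in means | yes |
| Non-normal: rank-sum | mean ± SD | tendency of one group's values to exceed the other's | no |

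A rank-sum result can be carried over to means only under a further assumption: that the two distributions have the same shape and differ by a constant shift. The article does not state this assumption. Its own t-test branch allows for unequal variances, which a pure shift would rule out.

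**2. The plan's own sample-size figures**

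The article takes its design inputs from "findings from a study that evaluated effect of chewing gum following pancreatic-duodenal surgery in Sweden" and concludes that "46 participants per group will be required". It then says: "On adjusting the sample size to the finite population and adding 10% to improve internal validity, the required sample size will be 52". The difference δ, the SD, the power and the size of the finite population are not given, so neither 46 nor 52 can be reproduced forward. Only the ratio δ/SD can be recovered, by inverting the article's formula N = 2 × ((z₁₋α/₂ + z₁₋β)/δ)² × S²:

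δ/SD = √(2/46) × (1.960 + z₁₋β), with √(2/46) = 0.2085.

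- 80% power assumed: 0.2085 × (1.960 + 0.842) = 0.584
- 85% power assumed: 0.2085 × (1.960 + 1.036) = 0.625
- 90% power assumed: 0.2085 × (1.960 + 1.282) = 0.676

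**3. Precision at the size to be randomised**

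The Abstract gives 52 patients in two groups and the randomisation section gives 1:1 allocation, so there are 26 per arm. The half-width of the 95% CI for a mean difference, in SD units, is

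t(0.975; 50) × √(2/26) = 2.009 × 0.2774 = 0.557.

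As a share of the implied difference this is 0.557/0.584 = 95%, 0.557/0.625 = 89% and 0.557/0.676 = 82%.

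**4. What a p value above 0.05 would and would not show**

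Power and non-significance at 26 per arm (t-test, normal data) come from the noncentral t distribution. The last three columns come from 400,000 simulated trials per setting. They give the share of non-significant results whose 95% CI still contains the implied difference.

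| Assumed design power | Implied δ/SD | Power at 26 per arm | Non-significant if δ is true | CI contains δ, if δ is true | CI contains δ, if δ/2 is true | CI contains δ, if no effect |
|---|---|---|---|---|---|---|
| 80% | 0.584 | 54.2% | 45.8% | 94.5% | 78.8% | 45.5% |
| 85% | 0.625 | 59.9% | 40.2% | 93.8% | 75.9% | 39.5% |
| 90% | 0.676 | 66.6% | 33.4% | 92.5% | 71.7% | 32.3% |

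Non-significant results therefore include trials that still admit the implied difference and trials that exclude it. An observed difference of exactly zero, with the SD as assumed, gives an upper limit of 0.557 SD, just short of 0.584 to 0.676. The p value does not separate these cases; an estimate with its interval does. These figures are for the t-test and serve only as a guide to precision. They do not measure the harm of the rank-sum wording, and reporting an interval changes neither the sample size nor the power.

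**The case against.** The strongest reply is that this is a condensed article. Naming an effect estimate and its interval is detail that the full protocol or analysis plan commonly carries, and neither is shown. The mean ± SD sentence is a general descriptive convention, and nothing says it is the only output. Standard t-test output already includes the difference and its interval. Group means, SDs and numbers would let anyone compute a mean difference with a CI, and the article commits to placing the data in a repository, from which any contrast could be derived.

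Most of this stands. The absence of a named confidence interval is not, by itself, an error, and it would be wrong to say that later researchers would have no usable effect size. What the reply does not reach is the stated text. The article itself assigns a comparison of means to the rank-sum test and keeps mean ± SD on that branch. There, t-test output is not the source of the result, and means and SDs do not yield the shift that belongs to the rank test.

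Several stronger readings are tempting, and the documents do not support them:

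- **That a null result is likely.** If the implied benefit is real, non-significance occurs in about 33% to 46% of trials under the assumed design powers. It becomes likely (78% to 82%) if only half that benefit is real.
- **That a null result would be taken to mean gum has no effect.** No section says so. The Discussion acknowledges the small sample and looks to larger trials.
- **That a non-significant result always remains compatible with the planned benefit.** The last column of the table shows otherwise: with no true effect, most such intervals exclude it.
- **That the Discussion's aim must be withdrawn.** "This protocol seeks to generate level one evidence regarding the role of chewing gum in resolution of ileus" expresses an aspiration about design and contradicts nothing in the analysis section.

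**Conclusion.** The point holds as a minor one. On the non-normal branch the article states wrongly what the rank-sum test compares, and it pairs that test with a summary that does not belong to it. It affects the primary outcome and length of stay, and only if the normality check sends the analysis down that branch. The documents give no data from which to judge how likely that is.

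The practical weight comes from limited precision. An interval half-width of 0.557 SD against an implied difference of 0.584 to 0.676 SD means that significance alone tells a reader little about the size of the effect. This rests on a two-sided 5% level, 26 analysed per arm, approximately normal data, and an assumed design power of 80% to 90%. The reduction from 46 per group to 52 in total is a separate sample-size matter; it enters here only because it sets the precision. No conclusion about how the investigators would interpret a null result follows from the text.

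**What to change.** In the data processing and analysis section:

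1. Delete the phrase that gives comparison of means as the purpose of the rank-sum test.
2. Let the summary follow the test: mean ± SD where the t-test is used, median and interquartile range by group where the rank-sum test is used.
3. Name the matching estimate for ileus duration and hospital stay. Suggested wording: *The effect will be reported as the gum-minus-control mean difference with its 95% confidence interval where the t-test is used, and as the Hodges-Lehmann shift with its 95% confidence interval, together with group medians and interquartile ranges, where the rank-sum test is used.*

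The Hodges-Lehmann estimate is the median of all pairwise gum-minus-control differences. Its usual interval goes with the rank-sum test under a shift model, and that assumption should be stated beside it.

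The cost is a change of wording and a little extra analysis work on the rank-sum branch. Sample size, significance level, power and trial conduct are unchanged. The change should be made before the outcome data are analysed.

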**Methods::**

This will be a randomised controlled trial done in 3 hospitals. Fifty-two patients will be randomised to 2 groups. Group A will receive chewing gum in addition to routine care, whereas group B will receive routine care only. The duration of post-operative ileus in the two groups which is the primary outcome, will be compared using the independent samples t-test in SPSS version 22. The length of hospital stay, in-hospital morbidity and mortality will be the secondary outcomes. This trial has been approved by Kampala International University research and Ethics committee (Ref No. **KIU-2021-60**) and Uganda national council of science and technology (Ref No. **HS1665ES**). Retrospective registration with the research registry has also been done (UIN: researchregistry8565).

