### Sampling technique, randomization, concealment allocation and blinding

Permuted balanced block randomization will be conducted by the study supervisor to generate a random sequence of numbers to represent the two groups in an equal allocation ratio of 1:1. The random numbers will be labeled on concealed envelopes. The sealed envelopes will contain a folded opaque paper with letter A or B representing (chewing plus routine care) and (non-chewing plus routine care) groups respectively so that its not possible to deduce the assignment group based on random sequence numbers by the allocating team (research assistants). In addition, the envelope will have a similar stamp on the seal to be able to deduce possibility of breach of protocol (premature opening of the envelope). At this time both consent for surgery, information about the study and or consent to participate in the study will be obtained in writing at the emergency department. This is to avoid bias of recruiting participants after knowledge of intra-operative findings and to enable pre-operative care standardization between groups. The allocating team (trained research assistants) will give the envelope to the eligible participant 2 hours prior to surgery when a diagnosis of gut perforation is made from the radiological findings. The envelope will remain sealed until the patient enters the operating room and the participant will be unblinded just before induction of anesthesia where an instruction will be issued regarding chewing or not chewing any gum post-operatively. At this point an additional number either H, F or K will be added to the sequence number on the envelope to form participant identification number (PIN) to represent HRRH, FRRH, KIUI-TH for tracking records of recruitment and representation from each hospital. The outcome assessors (attending physicians) will be blinded throughout about the ongoing study since chewing gum is not known to cause adverse effects that would warrant un-blinding. The recruiting team will be totally different from the outcome assessors.

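### Morbidity is graded on an ordered scale, but the planned chi-squared test ignores order, and the protocol does not say whether grades or any/none are compared

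*Protocol article*

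**What the plan says.** Morbidity and mortality are secondary outcomes (Abstract, Methods): "The length of hospital stay, in-hospital morbidity and mortality will be the secondary outcomes". The Study variables section says that morbidity "will be reported in accordance with the Clavien Dindo classification 2004" and lists four grades of rising severity, ending with "IV: Life threatening complications eg atleast one organ failure requiring ICU admission". It defines no any-versus-none version. Mortality is named beside morbidity as an outcome of its own.

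The Data processing and analysis section gives one test for both: "To compare the in-hospital morbidity and mortality, the chi squared test will be used". Significance is set for every comparison in the same way: "All analyses will be performed at 95% confidence level and a p value ≤0.05 will be considered significant". For time to resolution of ileus and length of stay, the same section plans a normality check, a variance check and a Mann-Whitney fallback. For morbidity it names no ordinal method and does not say which form of the variable enters the test.

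**The concern.** A Pearson chi-squared test gives the same result if the grades are relabelled in any order. A general move from grade III to grade I therefore counts no more than an arbitrary reshuffling of the same size. Spread over five levels, the table is also sparse at this sample size.

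At stake is one of the trial's three specific objectives. If chewing gum moved complications consistently up or down the scale, a test across unordered grades would be less likely to show it than a rank test on the same data. The form of the variable also changes the result, and as written it could be settled after the data are seen.

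**Working it through.** **Inputs from the protocol article.** Total 52 (Abstract: "Fifty-two patients will be randomised to 2 groups"), allocated "in an equal allocation ratio of 1:1", so 52 / 2 = 26 per arm. Significance level 0.05, two-sided, since the sample-size formula uses Z at 1 − α/2. Adding no complication to grades I to IV gives 5 ordered levels. No morbidity rate and no power for morbidity is stated, so there is no figure of the plan's own to reproduce.

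**Step 1: expected counts, by arithmetic.**
- With equal arms, the expected count in each arm for a level is half that level's total. It is below 5 whenever fewer than 10 of the 52 patients fall in the level.
- For all five levels to reach 10, 5 × 10 = 50 of the 52 patients are tied up. Each level must then hold 10 to 12 patients, which is an almost even split.
- The average expected count in a 2×5 table is 52 / 10 = 5.2.

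**Step 2: expected counts, by simulation** (40,000 trials per scenario, 26 per arm). With five levels, at least one expected count is below 5 in over 99% of tables, even with a uniform control distribution. More than 20% of expected counts are below 5 in 76% to 100% of tables. With four levels, 85% to 99% of tables have an expected count below 5.

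**Step 3: power.** The control distributions are assumptions. The other arm is shifted toward milder grades by a common odds ratio (proportional odds). Each cell shows power in % for chi-squared by grade / tie-corrected rank-sum / chi-squared on the lowest level versus the rest. The Monte Carlo standard error is at most √(0.25 / 40,000) = 0.25 percentage points.

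| Control distribution (none/I/II/III/IV, %) | OR 2 | OR 3 | OR 4 |
|---|---|---|---|
| 50/15/18/10/7 | 12.1 / 24.5 / 23.4 | 25.5 / 48.7 / 48.2 | 38.3 / 65.2 / 65.4 |
| 30/20/25/15/10 | 14.6 / 27.5 / 23.5 | 33.5 / 56.8 / 48.4 | 50.9 / 75.6 / 67.2 |
| 70/10/10/6/4 | 6.8 / 18.3 / 19.5 | 12.7 / 34.4 / 36.4 | 18.3 / 46.6 / 48.7 |
| 20/20/20/20/20 | 15.8 / 28.2 / 20.4 | 36.0 / 58.4 / 45.2 | 54.0 / 77.5 / 65.2 |
| four levels, 25/35/25/15 | 17.0 / 26.9 / 22.2 | 38.2 / 56.3 / 48.0 | 57.5 / 75.4 / 67.3 |

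Ratio of graded chi-squared to rank-sum power: 0.37 to 0.70 over the five-level rows at OR 2 to 4. With OR 5 and the four-level row added, the range is 0.37 to 0.82.

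Ratio of any/none chi-squared to rank-sum power: 0.72 to 1.06. It falls to about 0.6 or lower where few patients are free of complications and the shift is toward worse grades.

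**Step 4: false positives.** With no difference, the graded chi-squared rejects in 2.8% to 5.1% of trials and the rank-sum test in 4.8% to 5.1%. Sparsity makes the graded test conservative in some scenarios. It does not inflate the error rate.

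**Step 5: a case that goes the other way.** With control 50/15/18/10/7% against 50/35/2/2/11%, a difference with no consistent direction, chi-squared has 51% power and the rank-sum test 8%.

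**Step 6: mortality.** In the 2×2 table an expected count is below 5 whenever fewer than 10 of 52 patients die (10 / 52 = 19%). Even so, the exact size of the uncorrected chi-squared test at 26 per arm is at most 5.6% for event rates of 3% to 40%, against at most 2.8% for Fisher's test.

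**The case against.** The strongest reply is that the article never says the chi-squared test runs across grades. Grading is tied to how morbidity is reported, and the definition of morbidity as a deviation from the expected course fits a yes/no variable beside yes/no mortality. On that reading order and graded sparsity do not arise, and the power loss is small or nil in most scenarios. This stands. It is why the point is worded conditionally. But no yes/no version is defined, and such a comparison would set aside the grades the trial collects.

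A second reply is that this is a condensed article, and coding details and small-count fallbacks belong in an analysis plan that is not shown. That holds for a missing fallback, which is not raised as a fault. The test itself is a choice the article makes and can be assessed.

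Third, a rank test is not always better. Step 5 shows a reversal, so a reader should not infer that chi-squared is the least sensitive test available. Nor can a fixed loss such as half the power be read from the protocol, which gives no rates. That figure describes only some assumed distributions with modest shifts.

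A reader might also infer that deaths are lost because the listed grades stop at IV, or that chi-squared is unsound for mortality. Mortality is a separate outcome with its own comparison, so no death goes uncounted. Step 6 shows that the 2×2 test behaves acceptably. Placing death at the top of the scale, or using Fisher's test, is a matter of preference.

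**Conclusion.** The point holds in a limited form, as a minor improvement. The protocol records an ordered outcome, names a test that ignores order, and leaves the tested form of the variable open. If the grades are tested, small expected counts are almost certain at 26 per arm, and power is about 0.4 to 0.7 of a rank-sum test for a consistent shift with an odds ratio of 2 to 4 (0.37 to 0.82 across all scenarios tried). If any/none is tested, little power is lost in most scenarios, but the severity information is unused.

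The size rests on assumed grade distributions and on proportional odds. The sparsity follows from the sample size and the number of levels alone. The consequence is modest: the outcome is secondary, the primary comparison is untouched, and even the rank-sum test has only 18% to 28% power at an odds ratio of 2.

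**What to change.** In the Data processing and analysis section, replace the sentence on morbidity and mortality with wording such as: each patient's highest Clavien-Dindo grade (none, I, II, III, IV) will be compared between groups with the Mann-Whitney test, or with a proportional-odds model reporting a common odds ratio and 95% confidence interval; mortality will be compared separately in a 2×2 table and reported as counts with a risk difference and 95% confidence interval.

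If any-versus-none is what was meant, say so and define it.

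The cost is a sentence or two. The data, the sample size and SPSS 22 stay as they are, and the Mann-Whitney test is already in the plan for other outcomes. The price is lower sensitivity to a difference between grades that has no consistent direction. A table of grade frequencies by group would let readers see such a pattern.
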